- f) Follow up and any mandatory restrictions of people confirmed by PCR: All people with confirmed positive COVID-19 by RT-PCR to isolate for 10 days. After the isolation period, tested using professional Ag-RDT. If test is positive treat as having confirmed COVID-19 and manage accordingly. If test is negative, treat as negative.
- g) Contact tracing (32): All close contacts should quarantine for 10 days from the day of the person testing positive. If any close contact / family member develops any symptoms it is not necessary for them to be tested as well. They should be treated as if they are positive.

Antivirals are not yet available in Malawi, but are being introduced to 5 treatment centers through a Unitaids-sponsored initiative. Treatment eligibility criteria have not yet been finalized at the time of writing (Sept 2022).

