**Table 2. Proctors' implementation outcomes**

| Implementation outcome | Level of analysis                                                  | Available measurement                                                                                                                                                 |
|------------------------|--------------------------------------------------------------------|-----------------------------------------------------------------------------------------------------------------------------------------------------------------------|
| Acceptability          | Participants across all use cases
+ 2 implementers per use case | Semi-structured interviews                                                                                                                                            |
| Adoption (uptake)      | PSI programme                                                      | Programme data for each use case: 
 
• Number tested
 
• Number linked to care
 
• Number receiving care
 
 |
| Appropriateness        | Participants across all use cases
+ 2 implementers per use case | Semi-structured interviews                                                                                                                                            |
| Costs                  | Costing data across all use cases                                  | Costing and cost effectiveness study
Health system, user costs and societal downstream costs.                                                                      |
| Feasibility            | Participants across all use cases
+ 2 implementers per use case | Semi-structured interviews                                                                                                                                            |
| Fidelity               | Participants across all use cases
+ 2 implementers per use case | Semi-structured interviews                                                                                                                                            |
| Penetration            | PSI programme                                                      | Scaled to other programme sites                                                                                                                                       |

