### Methodological approaches

We will cost the OPD, outbreak and secondary distribution use cases using the iDSI Reference Case for economic evaluation guidelines (i.e., one-off testing models). Health care worker regular self-testing is explicitly **excluded**. The costing will be conducted from a societal perspective using ingredients-based costing approach. We will combine top-down and bottom-up costing approaches:

The bottom-up approach will include a time and motion costing approach aimed at observing staff time allocation on a typical workday, (12 providers in OPD and outbreak investigations), given there are no staff time equivalents with the secondary distribution model, totalling 24 providers.

Time and motion refer to providers working on multiple activities across all use cases. For example, a provider conducting both self-testing and PCR in a healthcare facility. Such a provider will be observed using time and motion studies to determine allocation of personnel time to professional use testing and PCR. The time and motion costing approach is not a new study in its own right, but a method of cost data collection as part of the cost and cost effectiveness component of the project. Written consent will be obtained ahead of the time and motion observations.

We will further conduct exit interviews on 60 purposively selected testers across the OPD, outbreak and secondary distribution use-case. These will be done at exit of the process and will be aimed at collecting costs of accessing COVID-19 testing. We will ask participants to estimate the amount of time taken and costs incurred to access testing. This will enable the estimation of opportunity cost to test both as direct out-of-pocket payments (direct costs) and lost income (indirect costs).

Since we are only interested in costs of accessing testing, we will not include any additional downstream costs including household costs. Written informed consent will be obtained from all participants before the interviews.

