## Outcomes

- i. Cost per kit distributed
- ii. Cost per kit used
- iii. Cost per positive patient diagnosed
- iv. Cost per positive patient diagnosed and linked to prevention and care
- v. Cost per COVID-19 infection and death averted
- vi. Cost of scaling-up COVID-19 self-testing

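### Section 5.5 calls the costing societal but excludes downstream and household costs, which contradicts Table 2 and leaves cost per infection and death averted with a numerator that stops at the test.

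*Protocol*

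**What the plan says.** Protocol section 5.5, Methodological approaches, sets the perspective: "The costing will be conducted from a societal perspective using ingredients-based costing approach". Later under the same heading, after describing the client exit interviews, it sets a limit. Giving as its reason that interest is confined to what it costs to get tested, it says "we will not include any additional downstream costs including household costs". The client costs that are collected are out-of-pocket payments and lost income, both tied to getting a test.

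Table 2 in section 5.4 gives the scope of the same costing work as "Health system, user costs and societal downstream costs".

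The outcome list in section 5.5 has six items. Item iv is "Cost per positive patient diagnosed and linked to prevention and care", item v is "Cost per COVID-19 infection and death averted", and item vi is the cost of scale-up. Objective 3 of section 5.5 plans economic modelling of impact, and the recruitment text there says that the study's costs and their components will go to outside modellers.

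On the policy background, section 2.6 reports the current national guidance: "All close contacts should quarantine for 10 days from the day of the person testing positive". Section 2.7 presents contact self-testing, fully costed, as evidence on whether a less blanket approach to contacts could be considered. Section 5.1.4 names economic exclusion as a possible harm of presuming every contact positive.

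**The concern.** A societal perspective counts costs whoever bears them. A costing that stops at the provider's cost of testing plus the client's cost of reaching the test is a narrower thing and needs a narrower name. Here the label and the exclusion stand under one heading, and Table 2 promises what the exclusion removes. An analyst cannot follow both and would have to choose, possibly after seeing data.

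The choice matters most for outcome v. Infections and deaths are averted by what happens after a test: isolation, masking and care. If the numerator ends at the test, the ratio counts downstream benefit without the downstream resources that produce it, and may still be reported to the Ministry of Health as societal. It also matters for the section 2.7 question, because quarantine of contacts is one of the costs that differ between presuming all contacts positive and testing them.

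**Working it through.** This is mainly a comparison of text. The protocol gives no cost-effectiveness figure to reproduce.

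**Scope, place by place**

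| Place | What it commits to |
|---|---|
| 5.5 Methodological approaches, perspective sentence | Societal |
| 5.5 Methodological approaches, exclusion sentence | Testing-access costs only; downstream and household costs out |
| 5.4 Table 2, Costs row | Downstream societal costs in |
| 5.5 Outcomes, item v | A ratio whose denominator is a downstream effect |
| 5.5 Objectives, item 3, and the hand-off to modellers | Modelling planned; no downstream cost input named |

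The second row conflicts with the first and directly contradicts the third. The fourth row cannot carry the societal label under the second unless the fifth supplies the missing costs, and the protocol does not say that it does.

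**What is collected**

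- Provider side: staff time, overheads, equipment, consumables and test costs (sections 5.1.2, 5.1.3 and 5.5).
- Client side: payments and income lost in getting a test (section 5.5).
- Secondary distribution: the patient cost tool is aimed at the index case's cost of delivering kits, and contacts are never telephoned (section 5.1.4).
- Index follow-up: section 6.2 says that the telephone interview records, at household level, the steps taken after testing, isolation among them. These are steps, not costs or days.

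No cost tool described in the protocol covers care costs, or work lost during isolation, quarantine or illness.

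**Gross scale of the contact quarantine item**

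Inputs: about 30,000 screening tests, 2% positive, and 3 household plus 2 other close contacts per index case (5.1.4 Sample size); 10 days of quarantine (2.6).

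- Index cases: 30,000 × 0.02 = 600.
- Contacts: 600 × (3 + 2) = 3,000.
- Contact-days: 3,000 × 10 = 30,000, or 50 per index case.

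(That this equals the number of tests is coincidence: 0.02 × 5 × 10 = 1.)

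This is an upper bound on the burden under existing guidance. It assumes that every index case is found and every contact quarantines for the full period. The index cases' own isolation, 600 × 10 = 6,000 days, is left out because section 2.6 requires it whether or not contacts are offered kits.

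**The case against.** The strongest defence is that the exclusion sentence sits between the exit-interview description and the consent statement for those interviews. It could therefore limit only what the 60 clients are asked, not what the whole evaluation counts. Outcome v cannot come from exit interviews and must be a model output; section 2.3 plans to estimate prevention and care impacts; and model inputs are commonly left to an analysis plan that is not shown here.

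Part of this stands: the modellers could bring downstream costs from elsewhere, so it is not certain that the final ratio would lack them. It does not remove the conflict. The sentence gives as its reason that the team's interest is confined to testing-access costs, and neither objective 3 nor the hand-off text names a downstream cost. Table 2 still contradicts the sentence on either reading.

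Other points of the defence limit what can be claimed:

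- A reader might infer that lost income is ignored altogether. It is not, since income lost while getting tested is collected.
- A reader might infer that nothing is known about contacts' isolation. Section 6.2 shows that uptake of isolation is recorded.
- A reader might infer that quarantine is the main stake in contact self-testing. Section 2.7 also names early diagnosis for antivirals and peak testing capacity, so quarantine is one relevant cost difference and its rank is not established.

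**Conclusion.** The protocol is inconsistent as written. The societal label in 5.5, the exclusion in 5.5 and the Costs row of Table 2 cannot all hold, and outcome v has no stated source for the costs that a societal ratio needs. This rests on reading the exclusion sentence by its own stated reason, and on no downstream input being named in the protocol.

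The documents do not allow the effect on the ratio to be sized. It is tempting to read the 30,000 contact-days, or 36,000 person-days with index isolation added, as the amount of the error. Neither is. Both are gross burdens under full adherence, whereas a cost per infection averted depends on the difference between strategies, and section 5.1.4 says that contact tracing has been abandoned in practice.

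Nor do the documents support one general statement about direction. If self-testing replaced quarantine of contacts, omitting the days avoided would understate a saving in that model. Omitting isolation of extra positives found in outpatient or outbreak testing would understate a cost in those models. A reader might also infer that comparisons with published societal ratios would be spoiled, but the protocol plans none; its comparators in section 2.3 are no alternative testing, NAAT and professional Ag-RDT.

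**What to change.** Reconcile Table 2 with the perspective sentence, the exclusion sentence and the outcome list in section 5.5, in one of two ways.

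(a) Restate the perspective in 5.5 and Table 2 as provider plus client testing-access costs. Keep outcomes i to iv and vi. Drop outcome v, or label it as excluding downstream costs. Outcome vi is a scale-up cost and the exclusion gives no reason to lose it. This costs wording only.

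(b) Keep outcome v and the societal label. State that the modelling adds isolation or quarantine time, lost income and care costs, and name the source of each. The index follow-up described in section 6.2 can inform how often contacts isolate; days and unit costs would need their own source. Confine the exclusion sentence to the exit interviews. This costs some extra modelling input.

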### Recruitment and consenting process

*Participant interviews:* The project coordinator will liaise with the recruitment site leadership to identify participants for all costing components. All those who consent to participate will be interviewed on site by a research assistant after their testing is completed. A small subsample will also be observed accessing the services from arrival at the centre to understand the patient pathway. We aim to recruit twenty participants for interviews per one-off testing use case. The secondary distribution of test-kit participants will be consented with written informed consent

before they leave the clinic, and the interview will take place on day 14. Recruitment and consenting for participants identified during implementation of study interventions will also be completed by the research assistant soon after receiving the testing at the recruiting site.

*Provider interviews and observations:* For use cases where testing will be happening even on weekends, the sample will be split to 10 observations on a weekday and 10 observations on a weekend. Half of the observations will be in the morning and the other half in the afternoon to ensure we are observing different type of clients.

All our costs and the associated ingredients and allocation factors will be shared with mathematical modellers from the London School of Hygiene and Tropical Medicine (LSHTM) and the Health Economics and Epidemiology Research Consortium for additional economic modelling.

## Outcomes

- i. Cost per kit distributed
- ii. Cost per kit used
- iii. Cost per positive patient diagnosed
- iv. Cost per positive patient diagnosed and linked to prevention and care
- v. Cost per COVID-19 infection and death averted
- vi. Cost of scaling-up COVID-19 self-testing

## 5.6. Clinical aspects and PPE

Any of the use cases who test positive for COVID-19 will be notified of their results and managed according to disease severity as per available local guidelines. Asymptomatic cases will be advised to self-isolate, monitor for COVID-19 symptoms, and report to the nearest health facility if symptoms emerge or worsen. COVID-19 positive cases with symptoms will be assessed for risk factors and severity (mild, moderate or severe) and referred to collaborating health facility for supportive treatment as required. All positive cases shall receive two KN95 masks for themselves and a pack of surgical masks to offer to their contacts. They shall also be advised on COVID-19 prevention measures including the proper use of face masks, social distancing, hand hygiene, and cough and sneeze etiquette.

## 5.7. Study period

**Figure 3:** project timelines

| Activity                                                                  | 2022 |    |    |    |
|---------------------------------------------------------------------------|------|----|----|----|
|                                                                           | Q1   | Q2 | Q3 | Q4 |
| Protocol and tools development                                            |      |    |    |    |
| Ethics Approvals                                                          |      |    |    |    |
| Staff hiring & training                                                   |      |    |    |    |
| a. Facility-based Ag-RDT CV19 interventions                               |      |    |    |    |
| i. Intensified diagnosis and screening in HCWs                            |      |    |    |    |
| 1. Diagnostic HCW clinic, risk-based home-management                      |      |    |    |    |
| 2. Twice weekly self-testing for early diagnosis                          |      |    |    |    |
| ii. Increased capacity and efficiency in OPD                              |      |    |    |    |
| 1. Systematic screening for CV19 symptoms + diagnostic testing            |      |    |    |    |
| 2. Add self-testing to improve surge management/efficiency                |      |    |    |    |
| 3. Secondary distribution of self-test kits: contacts                     |      |    |    |    |
| b. Early diagnosis in communities                                         |      |    |    |    |
| i. Outreach testing: suspected congregate outbreaks                       |      |    |    |    |
| 1. Provider-delivered Ag-RDT testing                                      |      |    |    |    |
| 2. Add community-led self-testing to increase timeliness/sustainability   |      |    |    |    |
| c. Safer and more affordable cross-border travel (all provider-delivered) |      |    |    |    |
| i. Evaluate Ag-RDT vs NAAT in returning travelers                         |      |    |    |    |
| ii. Add Ag-RDT services/masks to land borders                             |      |    |    |    |
| Economics                                                                 |      |    |    |    |
| Dissemination                                                             |      |    |    |    |
| Publications                                                              |      |    |    |    |

## 5.8. Overall sample size considerations

For the non-randomized controlled study: with an assumed harmonic mean number of 20 and 35 HCWs (common standard deviation: 12) in SOC and the PCI arm confirmed (either by PCR or by repeat professional Ag-RDT) COVID-19 diagnosed within three months, 6 clusters per arm of ~100 HCWs each, the study will have 84.1% power to detect the stated difference of harmonic count of 15.

For components offering self-testing, we conservatively assume that 60% of participants will be willing to self-test for COVID-19 if offered. For the sample proportion to be estimated to within +/- 0.05 (5%) using the 95% confidence level, a sample of 369 participants would be required. Whereas for components offering professional COVID-19 Ag-RDTs we conservatively assume that 70% of participants in each of the targeted groups will accept to be tested for COVID-19. For the sample proportion to be estimated to within +/- 0.05 (5%) using the 95% confidence level, a sample of 323 participants would be required.

## 5.9. Data collection

### Process evaluation

A TIDieR (Template for Intervention Description and Replication) summary for each use case will be written up, ensuring that each use-case is reported to the minimum standard to ensure replicability, of interventions. To create the TIDieR framework, semi-structured interviews with the study

coordinators will be conducted, complemented by interviews with two implementers on the ground for each use-case.

Thereafter, the study shall use Proctor's framework for implementation outcomes to evaluate each use-case.

For the nonrandomized controlled study:

Brief baseline data will be collected at the time of written informed consent to participate in each of the 12 facilities. The primary outcomes will be based on incident diagnosis of COVID-19, with the aim being to increase early diagnosis in the self-testing facilities compared to a) pre-intervention rates through retrospective data extraction from HCW data from the facilities and prospective interviews with HCWs and b) between the two different testing strategies. Additional outcomes will be captured at exit interview, during which HCWs will be asked about any time off work, and reason for this (any positive COVID-19 tests or untested 'flu like illnesses and any quarantine due to close contact). An assessment of risk factors including vaccination history, and knowledge, attitudes, perceptions and practices relating to COVID-19 transmission and prevention will also be explored and compared by facility testing-strategies. Cost effectiveness analysis will be conducted as detailed in the economics section for this component of the project.

#### Overall data tools

Data tools for the different components of the project have been developed by the investigators. For the HCW component, potential participants shall be screened for eligibility (Appendix 7 - CH00: Eligibility screening) before recruitment. A structured questionnaire (Appendix 8 - CH01A :Healthcare workers baseline questionnaire) shall be used to collect data on the participants' demographic characteristics, assess their risk for severe COVID-19, knowledge on basic facts about COVID-19 and their practices and behaviours regarding COVID-19 prevention at baseline in both study arms. Another structured questionnaire (Appendix 9- CH02: Healthcare worker follow-up) shall be used to follow-up the participants monthly up to three months to find out if they had any COVID-19 symptoms over the past four weeks. For those who had the symptoms, we will ask about the management and care they received. After the three months follow-up period, a structured questionnaire (Appendix 10 - CH03: Healthcare worker exit) shall be used to conduct an exit interview where we will reassess the participant's risk for severe COVID-19, knowledge on basic facts about COVID-19, absenteeism from work due to COVID-19, their practices and behaviours regarding COVID-19 prevention, COVID-19 related stigma and discrimination, and experiences with COVID-19 self-testing.

For the PSI-led provider-delivered COVID-19 Ag-RDT testing at OPDs and congregate settings, eligibility screening shall be conducted using Appendix 11 (CP00) and Appendix 13 (CW00) respectively. Structured questionnaires (Appendix 12- CP01: OPD Questionnaire and Appendix 14 – CW01) shall be used to collect data on the participants' socio-demographic characteristics, assess for COVID-19 symptoms, willingness to test and follow next steps on COVID-19 prevention if positive.

For the contact tracing study, potential participant shall be screened for eligibility (Appendix 15 - CC00: Eligibility screening) before recruitment. A structured questionnaire (Appendix 16 - CC01:

baseline questionnaire for index case) shall be used to interview index cases who tested positive for COVID-19 from any of the use cases at time of testing positive. The questionnaire will collect information on social demographic indicators about the index, COVID-19 symptoms, risk and testing, and information about their close contacts. Another structured questionnaire (Appendix 17- CC02: Index case follow up questionnaire) will be used to interview index cases 7-14 days after recruitment to follow up on each of their listed contacts.

For the qualitative process evaluation study, semi-structured topic guides shall be used to interview clients from OPD, congregate settings (Appendix 18: Client process evaluation qualitative interview guide), implementers (study coordinators, investigators and frontline implementers) (Appendix 19 - CK01: Process evaluation among key informants) and HCW (Appendix 20 - Providers SSI topic guide) in PIC arm who would have completed the three months follow-up period to assess the acceptability, adoption, appropriateness, costs, feasibility, fidelity and penetration of the intervention.

For the cost and cost effectiveness study, a structured questionnaire (Appendix 22 - Facility costing data collection tool) shall be used to interview clinic managers on: costs of overhead supplies (utilities, facility supervision, administrative, cleaning, security and transport costs); and COVID-19 testing costs (Ag RDT or PCR). The tool shall also be used to assess rooms, equipment, furniture, staffing, consumables and equipment used for each COVID-19 testing service, and time and motion for staff providing COVID-19 testing services. A semi-structured interview guide shall be used to ask clients about the time spent at the clinic and any costs incurred in accessing COVID-19 testing.

For the costing component: We will conduct exit interviews (Appendix 23: Client cost exit questionnaire) on 100 purposively selected testers across all use cases. The exit interviews will be aimed at collecting costs of accessing COVID-19 testing. We will ask participants to estimate the amount of time taken and costs incurred to access testing. For the OPD model, we will collect the user costs before and after the intervention to allow for a before and after analysis. This will enable the estimation of opportunity cost to testing both as direct out-of-pocket payments (direct costs) and lost income (indirect costs).

